## Abstract

**Background:** This will be a before-and-after study nested within a randomized clinical trial. Its objective will be to analyze the effectiveness of a teleconsultation and validate a questionnaire for performing teletriage in dental urgency/emergency situations in children aged 3 to 13, whose parents will have signed a free and informed consent form, and who have had full access to the internet.

**Methods:** The Questionnaire for Teletriage of Emergencies and Urgencies in Pediatric Dentistry (QuesT-Odontoped)—will be validated by applying it to 140 randomized child parents/guardians. After validation, another 260 children seeking emergency dental care in the municipality of Carangola, Minas Gerais, Brazil, will receive a remote consultation, be randomized, and then allocated into two groups: G1, teleconsultation, and G2, teleconsultation and face-to-face consultation (immediately after the former) with a blinded evaluator, involving anamnesis and conventional clinical examination. The G2 sample will be used in the before-after study. Both groups will be followed-up for 7 and 14 days using pain and quality-of-life scales, applied at baseline and after each follow-up period. Clinical follow-up will be carried out after 12 and 24 months to assess the outcome of the tooth that had been indicated for treatment in the teletriage. The Mann-Whitney test will be used to assess pain; Student’s t test or the Mann-Whitney test will be used to assess quality of life and the number of missing teeth after 24 months; and Poisson’s regression analysis will be used to assess the influence of other variables. The significance level will be set at 5%.

**Conclusions:** In conclusion, this study expects to confirm the hypothesis that remote urgency consultation (teletriage), through a validated questionnaire, will be able to define the planning of the clinical situation, reducing the chance of displacements and progression of infection, helping to eliminate patient pain and discomfort.

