**Figure 3. f3:**
[figure not shown]
Inclusion of patients in the randomized control trial (before and after). G1, teleconsultation; G2, teleconsultation plus face-to-face consultation.

Patients in G1 and G2 will be followed up for seven and 14 days using specific instruments to assess the absence or presence of pain (Wong-Baker scale)
^
31
^ and quality of life, according to the child’s age (Child Perceptions Questionnaire, CPQ,
^
32
^ or Early Childhood Oral Health Impact Scale, ECOHIS).
^
33
^ In the case of urgencies involving teeth, a 12- and 24-month follow-up of the tooth reported in the teletriage will be carried out. The clinical criteria used to determine treatment success will be no fistula or exudate, no abscess, no painful symptoms, and no pathological mobility (
Figure 4).

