### Data collection

The data will be collected at different timepoints, as shown in
Table 1.

**Table 1. T1:** Data collection. G1, teleconsultation; G2, teleconsultation plus face-to-face consultation.

	Time +/ -	Timepoint	Research actions
Training of examiners/researchers	8 hours	t-1	The examiners/researchers will be trained to carry out the study, including a 4-hour training program for urgencies of dental origin in children, and a 4-hour calibration program for questionnaire application.
Inclusion criteria - Quest - Odontoped	12 months	0	The parents/guardians of children with dental pain, who seek care at the University of São Paulo School of Dentistry, or at the University of São Paulo Health Superintendence (SAU), will receive the contact information for one of the researchers, complete with a telephone number, and information on the requirements for having a remote consultation.
Inclusion criteria (test and control groups) - Carangola, MG, Brazil	12 months	0	When arriving at a Basic Health Unit, a hospital or a dental clinic outside opening hours, the parents/guardians of children with dental pain will find a poster outside containing the contact information for one of the researchers, complete with a telephone number, the number of the ethics committee approval report, and the requirements for having a remote consultation.
Follow-up	1 week and 2 weeks	T1	Patients in G1 and G2 will be followed-up for 7 and 14 days using specific instruments to assess the absence or presence of pain (Wong-Baker scale), and the quality of life according to the child's age.
Follow-up	12 months and 24 months	T2	In the event of urgencies involving teeth, a 12- and 24-month follow-up of the tooth reported in the teletriage will be carried out. The clinical criteria used to determine treatment success will be no fistula or exudate, no abscess, no painful symptoms, and no pathological mobility.
Close-out	24 months	tx	Analysis and dissemination of research results.

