Before-and-after studies are considered observational studies, and use a preliminary diagnostic test to decide whether or not to treat a series of examined patients. These patients are submitted to another diagnostic method, and the treatment decision can then be revised. Since this before-and-after study is nested within a randomized controlled trial (RCT), the sample size calculation will take into account the primary outcome of the RCT and the two experimental groups. However, only the group evaluated using both methods (teletriage + face-to-face consultation) will be eligible for this study. Therefore, the before-and-after study sample will consist of 130 patients.

*Outcomes*

Primary outcome: the presence of dental pain in children and adolescents, considering independent samples.

Secondary outcome: quality of life (questionnaires according to age group) and tooth loss.

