### Data analysis

*Questionnaire validation*

The kappa coefficient (k) and content validity index (CVI) will be used to quantify the degree of agreement among experts during content validation. In order to assess the reliability of the instrument, the test and retest results will be evaluated using the intra-examiner agreement test (kappa test,
*k*), which is the appropriate statistical procedure to assess the reliability of categorical and nominal variables. The criterion validity will be analyzed by comparing the results of the teleconsultation with those of the face-to-face consultation using the chi-square test (χ
^2^). The significance level will be set at 5%, and the data will be analyzed using
Jamovi and
RStudio software.

*Randomized clinical trial*

Primary outcome: pain (Wong-Baker scale); secondary outcomes: quality of life (questionnaires according to age group) and missing teeth.

The primary outcome of the randomized clinical study will be any change in pain score observed at the 7-day and 14-day follow-up timepoints compared to baseline. This outcome comprises an ordinal qualitative variable; therefore, comparison between the teleconsultation and face-to-face consultation groups will be performed using the Mann-Whitney test.

Other secondary outcomes will be evaluated, such as the impact of treatments on oral health-related quality of life, and the number of missing teeth after the 24-month follow-up period. Differences between the groups regarding the final and initial scores of the questionnaires on oral health-related quality of life, as well as the number of missing teeth, will be compared using Student’s t test or the Mann-Whitney test, depending on the type of data distribution (normal or non-normal). In addition, Poisson’s regression analysis will be performed to assess the influence of other variables on the results. The significance level will be set at 5%, and the data will be analyzed using Jamovi and RStudio software.

*Before-after study nested within an RCT*

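### Quality of life is scheduled at baseline, day 7 and day 14, but the stated comparison uses only initial and final scores and does not say which day is final

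*Protocol article*

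**What the plan says.** Three places give the schedule. The Abstract says "Both groups will be followed-up for 7 and 14 days using pain and quality-of-life scales, applied at baseline and after each follow-up period". The Research design section says "Patients in G1 and G2 will be followed up for seven and 14 days using specific instruments", and lists quality of life, by an age-specific questionnaire, among those instruments. Table 1 in the Data collection section repeats that both groups are "followed-up for 7 and 14 days using specific instruments". No later quality-of-life assessment is listed.

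The Outcomes paragraph gives the standing of this measure: "Secondary outcome: quality of life (questionnaires according to age group) and tooth loss".

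The Data analysis section, under the randomized clinical trial, describes the comparison as "Differences between the groups regarding the final and initial scores of the questionnaires on oral health-related quality of life", tested by Student's t test or the Mann-Whitney test according to the distribution. For pain, the same section names both days: "any change in pain score observed at the 7-day and 14-day follow-up timepoints compared to baseline". The only other model for the trial is Poisson regression, where "regression analysis will be performed to assess the influence of other variables on the results"; it is not tied to the day-7 quality-of-life score.

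**The concern.** Three scores per child are collected and two enter the stated comparison. Two things follow from the text without any assumption about dropout. First, there is no stated between-group result for quality of life at day 7, although the questionnaire is given to both groups then. Second, the final score is not tied to a day, so two analyses fit the wording. If it means day 14, a child seen at day 7 and lost before day 14 drops out of the comparison. If it means the last available score, day-7 values of lost children are mixed with day-14 values of the others.

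A third consequence is conditional. If children doing badly at day 7 are lost more readily in one group than in the other, a comparison of those with a day-14 score is biased, and the day-7 score that could correct it is left out. The Research design section calls the trial noninferiority, so an error in favour of teleconsultation alone (G1) would be the unwelcome direction.

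**Working it through.** **1. Schedule against analysis**

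| Outcome | Measured | Stated between-group comparison |
|---|---|---|
| Pain (primary) | baseline, day 7, day 14 | change at day 7 and at day 14 |
| Quality of life (secondary) | baseline, day 7, day 14 | final against initial; day not given |

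The plan gives no standard deviation, effect size or sample size for quality of life, so there is no figure of its own to reproduce.

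**2. Possible bias of final minus initial (final = day 14)**

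From the Sample size section: 130 per group and a 10% dropout allowance, not divided by visit.

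Assumed: scores Y0, Y7 and Y14 are jointly normal with SD 1, higher meaning worse; there is no true group difference; loss after day 7 in G1 follows logit(p) = a + 1.0 × Y7; loss in G2 is unrelated to the score.

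Because loss depends only on Y7, and E(Y14 − Y0 | Y7) = (r(7,14) − r(0,7)) × Y7,

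bias = (r(7,14) − r(0,7)) × m, where m is the mean Y7 of the G1 children who remain.

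With a = ln(b/(1 − b)) for b = 0.10, 0.15 and 0.20, numerical integration over the normal distribution gives:

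| b | Lost in G1 | m | Bias, gap 0 | Bias, gap 0.2 | Bias, gap 0.4 |
|---|---|---|---|---|---|
| 0.10 | 13.4% | −0.119 | 0.00 | −0.024 | −0.048 |
| 0.15 | 18.9% | −0.164 | 0.00 | −0.033 | −0.066 |
| 0.20 | 23.9% | −0.204 | 0.00 | −0.041 | −0.082 |

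The gap is r(7,14) − r(0,7): for example 0.5 − 0.5, 0.7 − 0.5 and 0.7 − 0.3. Negative values favour G1. The range is 0.00 to 0.08 SD.

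If exactly 10% of G1 are lost after day 7, m = −0.091 and the bias is 0.2 × 0.091 = 0.018 to 0.4 × 0.091 = 0.036 SD. If the same mechanism and rate act in both arms, m is equal in both and the bias is zero.

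In a large-sample simulation with loss driven by day 7, a regression that used baseline and day-7 scores to predict the missing day-14 scores stayed within about 0.01 SD of zero in every setting tried.

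**3. Scale**

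With 130 per arm, two-sided 5% and 80% power (the plan's values for its primary outcome), the detectable difference is √(2/130) × (1.960 + 0.842) = 0.35 SD of the change score. At baseline to day-14 correlations of 0.2 to 0.5, that SD is √(2(1 − r)) = 1.26 to 1.00 score SDs, so 0.35 becomes 0.44 to 0.35 score SDs. The largest bias above is less than a quarter of that. Each instrument covers only part of the sample, so the detectable difference per instrument is larger still.

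**4. Precision of a baseline-adjusted analysis**

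For SD 1 and baseline to day-14 correlation r, the change score has variance 2(1 − r) and the baseline-adjusted score 1 − r². The ratio is (1 + r)/2.

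- r = 0.2: 0.96/1.60 = 0.60, or 40% lower.
- r = 0.5: 0.75/1.00 = 0.75, or 25% lower.

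**The case against.** Comparing a secondary outcome at its last visit with baseline is legitimate and limits the number of tests. An intermediate visit need not carry one, and pain, the primary outcome, is compared at day 7. The article is condensed, and a statistical analysis plan that is not shown may say how incomplete scores are handled or add a repeated-measures model. A linear mixed model also gives up the rank test that the plan allows for non-normal scores.

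Most of this stands as a limit on the point. What remains is that the comparison is stated, rests on two scores, and leaves the final day open, while the same section names both days for pain. That is a choice made in the text, not a detail left out.

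Three stronger readings are tempting and not supported:

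- A reader might size the bias from the day-14 score alone. Under the same loss assumptions that gives 0.06 to 0.14 SD, but the plan compares final with initial scores, for which the range is 0.00 to 0.08 SD.
- A reader might infer that the plan's result is biased. It is so only if loss depends on the day-7 score differently by arm, and the loss rates assumed here exceed the 10% total allowance.
- A reader might infer that a quality-of-life difference is most likely in the first week. The documents give no source for that.

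**Conclusion.** The point holds as a gap in a secondary analysis that is cheap to close. What is certain from the text is that day-7 quality of life has no stated between-group result and that the final score is not tied to a day. Day 14 is the natural reading, since no later assessment is listed, and on that reading a child with only a day-7 follow-up score contributes nothing.

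The bias is conditional and modest: about 0.00 to 0.08 SD in favour of G1 when loss depends on the day-7 score in G1 only, with log-odds 1 per SD, 13-24% lost in G1 and a correlation gap of 0 to 0.4. It is zero when loss acts alike in both arms or the two correlations are equal. All of these inputs except the group size are assumptions.

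**What to change.** In the Data analysis section, define the final quality-of-life score as day 14. For each age-specific instrument, fit one repeated-measures linear mixed model with the day-7 and day-14 scores as outcomes and with baseline score, group, day, group-by-day and baseline-by-day as terms. Include every randomised child with at least one follow-up score. Report the day-14 group difference as the main quality-of-life result and the day-7 difference from the same model. Keep the Mann-Whitney test on the day-14 change as a sensitivity analysis for non-normal scores.

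The cost is wording and a standard model that can be fitted in RStudio, which the plan already names; no visit or questionnaire is added. The model assumes data missing at random given baseline and day 7, and relies on approximate normality of residuals. In return, adjusting for baseline instead of taking a change score lowers the variance by about 25-40%, if the baseline to day-14 correlation lies between 0.5 and 0.2.

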## Introduction

Pediatric patients often have difficulty communicating their pain experience. It is not uncommon for parents to become aware of the problem and seek dental care only when the pain is intense and prolonged.
^
1
^ Pain symptoms—whether intense, prolonged, spontaneous or nocturnal—may suggest changes in the pulp-dentin complex. Dentoalveolar trauma is common in this population, and requires immediate communication between patients and dentists, which is essential for the decision-making process involved in providing the patient with the needed first aid.
^
2
^ In some cases, the prognosis will depend on prompt and appropriate intervention. However, dental emergency services are not available full-time in all geographic regions of a country. In Brazil, the social isolation measures adopted by the government as a result of the COVID-19 pandemic impacted the supply and demand of dental services, and any significant delay in adopting adequate measures for cases of dental emergencies/urgencies could compromise the final results and affect the patient’s quality of life.
^
3
^

Within the scope of the Unified Health System (SUS), urgencies represent an important opportunity to identify the individuals and locations that are most vulnerable. Ordinance GM/MS no. 2048 of November 5, 2002, of the Ministry of Health
^
4
^ provides that healthcare units should carry out patient reception and risk classification screening, and that this process should be conducted by a college graduate health professional, specifically trained for conducting these procedures. The regulation also recommends that pre-established protocols must be used in order to assess the degree of urgency of each patient. Today, however, the organization of dental emergency services is still based on the rationale of order of patient arrival, contrary to the hierarchization principle adopted by the SUS,
^
5
^ according to which the level of care required for each case must be identified, so that access to the required services can be ensured according to their complexity. In addition, patients rely on urgent care as a gateway to the system. The Ministry of Health sought to standardize patient reception in emergency services, and standardize the care process across the country
^
6
^ by means of a risk classification system. By doing so, it sought to improve the work process and enhance the effectiveness of healthcare services, provided in a humanized and patient-centered fashion, with the goal of ensuring more favorable outcomes. To this end, patient reception carried out by using a risk classification system and protocol ensures proper development of work processes, and improves the resolution capacity of health services. In addition, this system and protocol ensure prioritization of the more severe clinical cases, and an appointment scheduling based on patient demands.
^
7
^ Studies in the literature have used questionnaires to diagnose dental problems in children, such as caries lesions, dental calculus, gingivitis, dental fractures, and malocclusions.
^
8
^
^,^
^
9
^ However, to the best of our knowledge, none have proposed a model questionnaire for dental urgency cases, providing guidance for the proper referral of these patients.

Faced with the COVID-19 pandemic, each country has adopted different policies to resume its dental care services. The United Kingdom, for instance, chose to select cases through teledentistry, and to see only those patients requiring urgent treatment.
^
10
^ In Brazil, Resolution 226 of June 4, 2020,
^
11
^ and Ordinance No. 526 of June 24, 2020
^
12
^ of the Ministry of Health have regulated teleconsultation, telemonitoring, and teletriage procedures for dentists working in primary care. In this respect, teledentistry is a method of proven capability to provide healthcare to underserved population groups, or to those unable to attend a face-to-face consultation.
^
13
^
^‒^
^
16
^ Teledentistry may also be a viable alternative for assessing deferrable and non-deferrable urgency cases, by conducting a screening process based on available information and communication technologies, e. g. video calls or text messages containing photos.
^
17
^
^‒^
^
21
^ The World Health Organization (WHO)
^
22
^ recommended that its member-countries make use of telehealth as a strategy to improve the quality of services provided, even before the pandemic.
^
23
^

It is known that teledentistry has been considered a practical and economically viable strategy to provide healthcare to underserved populations, including the socially disadvantaged, those living in remote locations or rural areas, or those who simply do not have access to routine dental care.
^
24
^
^‒^
^
28
^ In this context, teletriage has been associated with streamlined patient referral, shorter waiting lines, and improved ordering of care priorities. Based on an accurate assessment provided by remote screening, patients can receive proper primary support in an appropriate and customized fashion, and be directed to telecare or to the dental office itself, when needed, thus minimizing unnecessary displacements and contamination risks.
^
29
^ However, consistent scientific evidence is still lacking on the advantages of teletriage in dentistry; therefore, further investigation into the possibilities of using telecommunication tools in the planning of health actions is warranted, particularly for the sake of municipalities that do not have the human resources to provide specialized care, and general populations that do not have access to a specialist.

### Objectives

The foremost aim of this study will be to analyze the effectiveness of teletriage and of an urgency/emergency risk classification system for children, compared to face-to-face consultation for these patients. Secondarily, other key issues will be investigated, as follows:
1 -validation of a questionnaire for dental urgency screening in children;2 -assessment of the level of agreement among diagnoses and risk ratings assigned to cases screened in person versus remotely;3 -proposal and testing of an oral health protocol for patient reception and risk classification for children seeking an urgency/emergency dental care service.

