**Figure 2. f2:**
[figure not shown]
Validation of the questionnaire applied in the study.

*Before-and-after study nested within a randomized clinical trial*

The present research project will consist of a randomized, controlled, noninferiority, and blinded (examiners) clinical study, with 260 children aged 3 to 13 years in dental urgency situations. All of the participants investigated will be users of Basic Health Units, hospitals or dental clinics, residing in the municipality of Carangola, MG, Brazil. A link providing access to the Telehealth and Teledentistry Center from the University of São Paulo School of Dentistry (Nutes/FOUSP) platform will be sent to each patient after said patient makes the first contact through

*WhatsApp*
, a messaging app. All patients will be previously evaluated by a previously trained researcher in a teleconsultation (“before”), and then randomized and divided into two groups: G1, comprising 130 patients seen via a teleconsultation, and G2, comprising 130 patients seen via a teleconsultation and also in person (
Figure 3). The face-to-face evaluation (“after”) will be performed by two researchers who will be blinded to the result of the teleconsultation, who will perform anamnesis and clinical examination using a specific dental record, and who will answer whether or not the patient’s case is an urgent situation at the end of the evaluation. The dental condition motivating inclusion of the patient in the study will be treated by the researcher, and any other patient needs will be seen to by referring them to the health unit where they were registered.

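### The RCT compares teleconsultation alone with teleconsultation plus an immediate face-to-face visit, not teletriage with face-to-face care as the aim and group labels imply

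*Protocol article*

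**What the plan says.** All references are to the protocol article.

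- **Aim (Objectives).** The study is to "analyze the effectiveness of teletriage and of an urgency/emergency risk classification system for children, compared to face-to-face consultation for these patients". Agreement between remote and in-person diagnoses and risk ratings is listed separately, as a secondary aim.
- **Arms (Research design, nested study).** "All patients will be previously evaluated by a previously trained researcher in a teleconsultation", after which the arms are "G1, comprising 130 patients seen via a teleconsultation, and G2, comprising 130 patients seen via a teleconsultation and also in person". The Abstract and the legends of Figures 1, 3 and 4 describe the arms in the same way. The Abstract places the G2 visit immediately after the call.
- **Framework (same section).** The trial is a "randomized, controlled, noninferiority, and blinded (examiners) clinical study".
- **Analysis (Data analysis, Randomized clinical trial).** For change in pain score at 7 and 14 days, "comparison between the teleconsultation and face-to-face consultation groups will be performed using the Mann-Whitney test".
- **Treatment (Research design, nested study).** "The dental condition motivating inclusion of the patient in the study will be treated by the researcher". The sentence follows the description of the G2 examination and names no arm. Criteria for treatment success at 12 and 24 months come next, and the Figure 4 legend on those criteria names both G1 and G2.
- **Paired study (Sample size; Data analysis, Before-after study).** The 130 G2 children, assessed by both methods, form the before-and-after sample. Its primary outcome is a change in the urgent or elective decision after the in-person consultation. The in-person examination is done by "two researchers who will be blinded to the result of the teleconsultation".

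**The concern.** The stated question sets teletriage against face-to-face consultation, and the analysis section labels the randomized groups accordingly. The arms differ in something else: whether an in-person visit is added to a call that everyone receives. Whatever the call does for every child, good or bad, is present on both sides and cannot be seen.

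The treatment sentence adds a second difficulty. If the researcher treats only G2, a pain difference at day 7 or 14 largely measures access to treatment. If G1 children are also treated in person, the two arms receive much the same care and similarity is partly built in.

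What is at stake is the reading of the pain result. The trial is declared noninferiority, so similar pain in G1 and G2 would be the favourable finding. With the current labels it could be taken to show that teletriage matches face-to-face care, which is not the comparison the arms make.

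**Working it through.** The plan gives no figure for this point, so the check is mainly a comparison of the stated question with the stated arms.

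**1. What each arm receives**

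| | Teleconsultation | Face-to-face visit by allocation |
|---|---|---|
| G1 (130) | yes | no |
| G2 (130) | yes | yes, immediately afterwards |
| Face-to-face only | no such arm | no such arm |

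Research design has the child evaluated by teleconsultation and then randomized. Assignment has the envelope opened just after the call starts. On either wording, both arms have the call.

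**2. What the contrast estimates**

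Write T for mean outcome under teleconsultation alone, TF under teleconsultation plus face-to-face, and F under face-to-face alone.

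- The RCT estimates T − TF.
- The aim, as worded, asks for T − F.
- T − F = (T − TF) + (TF − F).

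The last term is the effect of the preceding call in children who are then seen in person. No arm gives information on it. The RCT answers the worded aim on pain, quality of life and tooth loss only if TF − F is zero. The article does not state that assumption. The Abstract's conclusions expect the remote consultation to help relieve pain and discomfort, so the assumption should not be left implicit.

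**3. What the paired study covers**

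In G2, the same child has a remote decision and an in-person decision, the latter made without knowledge of the former. That compares the two triage decisions directly. Its outcome is a change of decision, so it does not supply the missing comparison on pain, quality of life or tooth loss.

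**4. Two readings of the treatment sentence**

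- *G2 only.* This fits the position of the sentence, directly after the G2 examination. It sits less easily with treatment success being assessed in both groups, and with an analysis of the impact of treatments on quality of life compared between the groups.
- *Both arms.* This fits the follow-up of both groups, but not a G1 defined as seen by teleconsultation.

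**5. Illustration of converging care**

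Input from the plan: a difference of 15 percentage points (Sample size, RCT). Assumptions: a share u of children would have the same in-person care in either arm (u is not given), and those children do not differ between arms.

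Overall difference = u × 0 + (1 − u) × d, so d = 15/(1 − u).

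- u = 50%: 15/0.50 = 30 points
- u = 80%: 15/0.20 = 75 points
- u = 85%: 15/0.15 = 100 points, the ceiling for a difference in proportions

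These figures show direction only. G2 is seen at once, while the timing of any G1 visit is not given, so children seen in person in both arms could still differ. The 15 points are also a difference in proportions, whereas the stated primary analysis is a Mann-Whitney test on change in score.

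**The case against.** A reader might infer that the study cannot answer its foremost aim at all. The documents do not support that.

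- The aim belongs to the whole study, which has three stages. The paired G2 study compares remote and in-person triage decisions directly, with blinded in-person examiners. It needs both consultations in the same child, so making G2 face-to-face only would remove its sample.
- The RCT can still show whether omitting the in-person visit worsens outcomes, which is a natural noninferiority question. Because the G2 examiners do not know the teleconsultation result, G2 approximates face-to-face care if the call changes nothing else. This stands as a possible interpretation, but it needs the unstated assumption: blinding protects the examiners' decision, not whatever the call may have changed for the family.
- The arms are disclosed openly and repeatedly, and calling G2 the face-to-face group can be read as shorthand. That is fair for the label in the analysis section, less so for the Objectives, where the comparator is the substance of the sentence.

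Two further inferences should be avoided. The Introduction's remark that triaged patients can be directed to a dental office is background on teletriage in general, not a trial procedure. It is no evidence of how G1 children are handled. The closing hypothesis in the Conclusions concerns the screening decision and makes no comparative claim, so it needs no correction on this ground.

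Finally, Figures 3 and 4 are not shown and the article condenses a fuller protocol, so the scope of treatment may be settled there. The treatment sentence is therefore ambiguous as printed, not proved contradictory.

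**Conclusion.** The point holds in a limited form. The randomized contrast is teleconsultation alone versus teleconsultation plus immediate face-to-face consultation. It does not estimate teletriage against face-to-face care alone on patient outcomes, as the Objectives and the group labels in Data analysis imply, unless the preceding call is assumed to leave G2 outcomes unchanged. The triage-decision part of the aim is met by the paired G2 data.

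The unclear reach of the treatment sentence leaves two different trials compatible with the text: one driven by access to treatment, one with largely similar care in both arms. No size can be attached from the documents, because the share of G1 seen in person is not given; the 30, 75 and 100 point figures are illustrations under assumptions.

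This matters because it changes what a pain result may be said to show. Patients are already being included (Study status; the article does not say for which stage), and in-person visits that are not recorded at the time may be hard to recover later.

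**What to change.** 1. In Objectives and in Data analysis (Randomized clinical trial), state the RCT contrast and the conclusion it permits as teleconsultation alone versus teleconsultation plus immediate face-to-face consultation. Assign the remote versus in-person decision comparison to the paired G2 data. If G2 is to be read as a stand-in for face-to-face care, state the assumption that the call does not itself change G2 outcomes.
2. Reconcile the treatment sentence in Research design with the definition of G1 and with the follow-up of treatment success in both groups. Which children are treated is for the investigators to state.
3. At the existing day 7 and day 14 contacts, ask in both arms whether any in-person dental visit or treatment took place, and when. Report this by arm beside the pain result, so that similarity arising from G1 children being seen in person can be recognised.

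The cost is some rewording and two added follow-up questions, with no extra patients, visits or arms. The drawback is a narrower claim for the RCT.
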